##### Resident-level data.

Resident data extracted from the PM system database and the 12-month baseline and 4-week intervention MDS (batch file) and EMR; each resident will be assigned a study ID number prior to data extraction. New PrU incidence will be collected during the intervention period. Baseline data will be collected for 12 months just prior to intervention launch and will consist of EMR, MDS, and PrU incidence (Table 2) data. Intervention data extraction (of EMR, MDS, and PM system data) will occur weekly during the intervention 4-week period. The PM system will schedule resident repositioning frequency and gather resident repositioning sensor data automatically according to NH standards of care. Data collected by each resident’s sensor will be automatically communicated wirelessly through a proprietary mesh network of relay antennas to the respective NH’s Central Monitoring Station containing turn management software. Wireless sensor data on all monitored residents will be stored by the PM system. The wireless sensor number will become associated with a resident study identifier to be created as described below. The study ID number will be used to facilitate data comparisons. Wireless sensor data for all monitored residents will be securely stored in the PM system database.

Bench testing and clinical trials of the PM system’s wireless sensor have demonstrated it to be a valid measure of active and passive movement (repositioning). The sensor’s sensitivity accuracy is +/− 2.5% consistent with the industry standard for a linear triaxial accelerometer. Studies and clinical data show that the device effectively detects position changes according to threshold parameters, like degree or angle of position change. Wireless sensor data on all monitored residents will be securely stored in the patient monitoring system database. Wireless sensor data along with other resident data, including EMR data, will be transferred to the researchers for analysis. Turn management software in the PM system displays each resident’s repositioning history and current positional status in an organized and simple way on strategically placed nursing station and hallway display screens, making staff aware when resident repositioning actions are becoming necessary or are overdue. The percentage of on-time repositioning will be calculated for the period during which the wireless sensor is worn.

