### The intervention

Elements of the intervention include a NH-wide assigned repositioning interval 2, 3, or 4-h) with repositioning of residents using viable VE mattresses. Monitoring and documentation of repositioning intervention will be accomplished with use of a PM system. Table 1 describes the protocol components in detail.

**Table 1 Tab1:** Protocol for implementation of intervention approach

Protocol Components	Rationale/Outcome	Persons Responsible	Time (Fig. 4)
(1) PrU Prevention and Study Protocol Education Content: Introduces all NH nursing staff to PrU etiology, evidence-based PrU prevention practices, benefits of repositioning, & EMR documentation. Outlines roles & responsibilities, staff work flow, & performance & documentation of movement of residents. Content includes NH-wide repositioning strategy & suggestions for best practice implementation with cueing every 2, 3, or 4 h (24 h/day, 7 days/wk) depending on NH’s hourly protocol. Delivery Strategies: • Researcher leads initial session containing videos embedded in PowerPoint overview with simulation of repositioning & documentation process, followed by questions & answers. • Reference cards provided to all staff summarizing PrU etiology & staff responsibilities in relation to study protocol, day-to-day procedures, & directions for carrying out the protocol & completing study measures & documentation.	Establish knowledge of PrU etiology prevention practices, & study protocol. Facilitate consistency in response to intervention protocols, safety, & group effectiveness. Encourage problem-centered thinking & learning by demonstration and return demonstration.	RNs, LPNs, NAs, NPs	Initial session week prior to repositioning protocol start; for new staff orientation: one 60-min session followed by one-on-one training as needed when working.

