#### Repositioning protocol

Residents who are in bed will be repositioned according to the predetermined NH-wide assigned repositioning interval of every 2, 3, or 4 h, and rotated from side to back to side. In accordance with International PrU prevention guidelines [13], residents will be positioned in the lateral position at no more than a 30^0^ tilt. While in the supine position, the head of the bed may be elevated during feeding, but the duration of elevation greater than 30^0^ will be limited to avoid exposure to friction and shear. Residents will wear pressure reduction boots if ordered by the NH; however, because there is no evidence that these perform better than elevating the heels using a pillow, the latter will be standard procedure in this study. According to NH policy, there is a standing order that nursing staff should assist non-bedfast residents while in the chair to stand/move/reposition each hour to relieve ischial pressure, preventive seating cushions will be used as necessary according to NH guidelines. PrUs resulting from sitting will appear on ischial tuberosities; these PrUs are clearly different from PrUs on the sacrum/coccyx, trochanter, and heels that occur when lying in bed. Repositioning devices (e.g., turning sheets or trapeze) will be used as appropriate to reduce friction and shear, and pillows and foam wedges will be used to maintain position according to international guidelines.

In NHs, up to 9% of long-stay residents spend the majority of most days in bed or in a chair in their room [38]. Bates-Jensen et al. found that most residents spent 17 h a day in bed [34]. We expect, however, that 90% of residents will be sitting for at least part of the day. Repositioning will occur during the time that residents are in bed. Figure 2 is a visual depicting the required assessment and repositioning safety and skin care check to be performed by nursing staff and the criteria that must be met at each decision point in implementing the repositioning protocol.

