**Fig. 3 Fig3:**
[figure not shown]
TEAM UP study high-level components diagram and key data sources

**Table 2 Tab2:** Summary of concepts and instruments / measurements used to collect data

Concept Measured	Measures / Instrumentation	Source (Fig. 3)
Cumulative incidence of (new) PrUs for pre-intervention (baseline) period	Cumulative Incidence rate = [(# of residents with 1 or more new PrUs during a 1-month period) ÷ (# of NH residents with 3 or more day stay)] × 100; calculated monthly to establish baseline over the 12-month period before each NH intervention begins.	• MDS 3.0 • NH self-report • EMR data extract
Cumulative incidence of (new) PrUs for intervention period	Cumulative Incidence rate = [(# of residents with 1 or more new PrUs during intervention period) ÷ (# of residents participating in intervention for 3 or more days)] × 100; calculated for the full 4-week intervention period.	• MDS 3.0 • NH self-report • EMR data extract
Braden Scale©	The Braden scale is being used per protocol by participating NHs to assess resident risk for PrUs at intervention start and weekly thereafter.	• EMR data extract
Repositioning frequency	The scheduled duration of time for a resident’s pressure exposure as reflected by the 2-, 3-, or 4-h time interval at which the resident is repositioned; each NH will be randomly assigned to one of the study’s 3 arms and will use a single NH-wide repositioning frequency.	• PMS Central Server containing Monitoring Management Software
Recorded repositioning frequency	The actual time interval at which repositioning occurs, as documented by the Leaf sensor; recorded in clock time hours and minutes, 24 h per day, from start to end of resident’s participation in the 4-week intervention. Repositioning activities of residents will be captured using the Patient Monitoring System; Admission, Discharge, Transfer (ADT) feed from NHS to Monitoring System enables a match for Study ID# to resident movement, which is required for resident tracking in the event of room change, discharge/readmission, or other events.	• PMS Central Server containing Monitoring Management Software
Repositioning protocol adherence: % agreement	Percentage of agreement between scheduled repositioning frequency and repositioning frequency recorded by wireless sensor: [(scheduled clock time - recorded clock time = # minutes difference) ÷ 60] × 100]; calculated for each resident’s repositioning episode.	• PMS Central Server containing Monitoring Management Software

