##### EMR integration of patient monitoring system and CSI procedures.

The EMR will be used to facilitate data collection and export of study-related data, which includes an interface with wireless sensor data. This approach eliminates costly labor-intensive, in-person fidelity checks and minimizes research burden on staff. Individual wireless sensors will communicate with wireless antennas placed throughout the NH, permitting resident monitoring in all NH areas. The patient monitoring system will allow us to ascertain repositioning protocol adherence by measuring consistency between scheduled, performed, and documented repositioning frequency with random weekly observational repositioning checks to ensure repositioning fidelity. With CSI and other resident data, medical severity components will be assessed by staff based on NH policies and procedures and monitored in relation to risk level.

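### The assigned interval governs bed time only, but the on-time percentage and recorded repositioning frequency also take in chair time, unless the software already removes it

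*Protocol article*

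**What the plan says.** **Where the interval applies.** The Repositioning protocol section ties the assigned interval to bed: "Repositioning will occur during the time that residents are in bed". For time out of bed it cites a standing order of the homes, the same in every arm, that "nursing staff should assist non-bedfast residents while in the chair to stand/move/reposition each hour". It also cites 17 h a day in bed for most residents and expects 90% to sit for at least part of the day.

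**Where delivery is measured.**
- Table 2, recorded repositioning frequency: "recorded in clock time hours and minutes, 24 h per day", over the whole of the resident's participation.
- Resident-level data: "The percentage of on-time repositioning will be calculated for the period during which the wireless sensor is worn". Under Methods, the sensor is worn throughout the intervention.
- Table 2, protocol adherence: "Percentage of agreement between scheduled repositioning frequency and repositioning frequency recorded by wireless sensor". This is calculated per repositioning episode, and no time window is given.
- The section on EMR integration describes antennas "permitting resident monitoring in all NH areas", and the staff education in Table 1 refers to "cueing every 2, 3, or 4 h (24 h/day, 7 days/wk").

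The section on the patient monitoring system says that body position is tracked and displayed. It does not say that upright time is removed from any summary, or that sitting up resets the turn clock.

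**The concern.** Two stated windows do not match. The intervention runs while the resident is in bed, but two fidelity summaries run over 24 h or over all the time the sensor is worn. For most residents, part of that time falls under a different, hourly rule that is common to the arms.

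The trial expects no difference between arms. Such a result is informative only if the arms really received different in-bed intervals. The Risk and challenges section relies on the sensor's time-stamped record for this, because staff documentation is thought unreliable. If chair time is mixed in, the level of a summary no longer tells the reader what was delivered in bed.

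**Working it through.** The article gives no adherence figure, so there is nothing to reproduce. The sums below illustrate what the stated windows could do.

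**Inputs from the article.** Interval i = 2, 3 or 4 h; 17 h a day in bed, hence 24 − 17 = 7 h out of bed; an hourly rule in the chair.

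**Assumptions.** Chair patterns are the same in each arm. The range of 15 to 22 h in bed and the in-bed on-time share s are ours.

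**1. On-time percentage with perfect in-bed delivery, chair slots counted as missed.** Scheduled slots over 24 h number 24/i = 12, 8 and 6. Those in bed number 17/i = 8.5, 5.67 and 4.25. The ratio is 17/24 = 71% in every arm. With 15 h in bed it is 15/24 = 62.5%, and with 22 h it is 22/24 = 91.7%.

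**2. On-time percentage with s = 60% in every arm, under four possible counting rules.**

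| Handling of the 7 upright hours | Formula | 2-h arm | 3-h arm | 4-h arm |
|---|---|---|---|---|
| (a) time counted as compliant | (17s + 7)/24 | 71.7% | 71.7% | 71.7% |
| (b) slots counted as missed | 17s/24 | 42.5% | 42.5% | 42.5% |
| (c) each hourly chair move an on-time episode | (17s/i + 7)/(17/i + 7) | 78.1% | 82.1% | 84.9% |
| (d) upright block one late episode | (17s/i)/(17/i + 1) | 53.7% | 51.0% | 48.6% |

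For example, (c) in the 2-h arm is (5.1 + 7)/15.5 = 78.1%. The true in-bed value is 60% throughout, so the level is wrong under every rule, upwards under (a) and (c) and downwards under (b) and (d). Arms that are truly equal look unequal only under the episode-based rules (c) and (d), and in opposite directions. Under (a) and (b) they stay equal.

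**3. Recorded frequency over 24 h.** The article fixes no summary of this record. If one took the mean interval, with full in-bed delivery and c moves registered per day in chair time, it would be 24/(17/i + c):
- c = 1: 24/9.5 = 2.53 h, 24/6.67 = 3.60 h and 24/5.25 = 4.57 h.
- c = 7 (every hourly move registers): 24/15.5 = 1.55 h, 24/12.67 = 1.89 h and 24/11.25 = 2.13 h.

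The reading exceeds i when c < 7/i, so even the direction of the error depends on c. Arm order holds, and so does the gap of 8.5 − 4.25 = 4.25 moves a day between the 2-h and 4-h arms.

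**4. Percent agreement.** It compares scheduled with recorded clock time, episode by episode. Chair time enters only if chair moves count as episodes. The Repositioning protocol section uses the same verb for chair moves, so the term does not settle this.

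**5. In-bed restriction.** Counting only in-bed slots gives 60% in every arm in step 2, over 8.5, 5.67 and 4.25 scheduled slots a day.

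**The case against.** The strongest reply is that the stated windows describe data capture, not denominators. Recording around the clock fixes no summary, and the wear-time clause may be there only to handle residents who refuse or remove the sensor. The only schedule in the system is the 2-, 3- or 4-h one, so on-time repositioning may naturally mean in-bed turns. How upright time is handled is software or full-protocol detail, and Figure 2 is not shown.

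Part of this stands. The article does not show that the software miscounts chair time, and an in-bed reading is possible. The mean intervals in step 3 concern a summary that the plan does not contain. But the article does state a window for the on-time percentage, and that window is wider than the intervention. The point is therefore more than a missing detail. If the software does set upright time aside, one sentence in Table 2 settles it.

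The article also plans "random weekly observational repositioning checks to ensure repositioning fidelity". These cover six residents a week for at least four weeks, and the Treatment fidelity section describes them as a check that the system detects turns. They give limited support on the interval delivered day and night.

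A reader might also infer that percent agreement is calculated over 24 h. The text does not say so; that measure is defined per episode, and its exposure to chair time is conditional.

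**Conclusion.** The point holds as a cheap improvement to the fidelity measures. The on-time percentage and the recorded frequency have stated windows that include time when the assigned interval does not apply. Unless upright time is already removed, their level need not reflect the in-bed interval delivered. The size depends on the counting rule: perfect delivery could read 71% (62.5% to 91.7% for 15 to 22 h in bed), and a true 60% could read anywhere from 42.5% to 84.9% at 17 h in bed.

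Two stronger readings are not supported:
- **That the record is biased between arms.** This appears only under some assumed episode-based rules, in either direction, and the article does not say which rule the software uses.
- **That the trial's main results are compromised.** The Aim 1 comparison is by assigned interval under intention to treat, and the models under Analysis and Statistical power use the repositioning schedule. None names these fidelity measures.

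**What to change.** Calculate the on-time percentage and the recorded interval over in-bed (non-upright) time, using the stored position data with a stated angle cut-off. Apply the same rule to the three homes already completed. Limit percent agreement to in-bed scheduled turns, and report upright time by arm so that readers can see whether chair patterns were alike. If the software already excludes upright time, say so in Table 2. Fix the rule before adherence is tabulated by arm, because the possible rules give different answers.

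The cost is the wording of three definitions and a filter on existing data, with no new data collection and no change in conduct. There is one small downside: a chest sensor may class some head-elevated bed time, which the protocol allows during feeding, as upright. That is why the cut-off should be stated.

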##### EMR integration of patient monitoring system and CSI procedures.

The EMR will be used to facilitate data collection and export of study-related data, which includes an interface with wireless sensor data. This approach eliminates costly labor-intensive, in-person fidelity checks and minimizes research burden on staff. Individual wireless sensors will communicate with wireless antennas placed throughout the NH, permitting resident monitoring in all NH areas. The patient monitoring system will allow us to ascertain repositioning protocol adherence by measuring consistency between scheduled, performed, and documented repositioning frequency with random weekly observational repositioning checks to ensure repositioning fidelity. With CSI and other resident data, medical severity components will be assessed by staff based on NH policies and procedures and monitored in relation to risk level.

##### Staff-level data.

The web-based survey will be administered electronically on-site with touch screen tablet, pre/post the 4-week intervention during the time the employee is at work. The Nursing Culture Assessment Tool (NCAT) [46, 47] survey contains 19-items and there are some demographic items (i.e., length of time employed, job category, age, gender, education level, shift), and will be administered pre/post intervention. At the time of survey data collection, data will be transferred through a secured server from which it will be downloaded into a database for statistical analysis. Data will be stored on the study’s secure encrypted drive (SED).

### Measures

The measures and time points at which data will be collected are summarized in Table 2, and Fig. 4 is the study timeline and data collection schedule.

**Fig. 4 Fig4:**
[figure not shown]
Study timeline and data collection schedule

#### Qualitative data collection procedures

##### Focus groups.

In three randomly selected NHs, one from each hourly repositioning protocol, focus group sessions (one for staff, one for residents) will be held to explore the intervention approach and implementation. There will be one group of NH staff (*n* = 6) and one group of NH residents (*n* = 6) per site. NH staff focus group discussion will be stimulated using semi-structured questions to gather participant perspectives on implementation challenges. Each session will last 30–45 min. At the start of all focus group sessions participants will be consented. All focus groups will be recorded and verbatim transcripts (with no participant identifiers) will be prepared for subsequent use in data analysis.

#### Analysis

##### Quantitative analyses.

We hypothesize that there will be no significant difference in PrU incidence between the 3 treatment arms in the study using three risk level groups: high risk (Braden Scale Score, 10–12), moderate risk (Braden Scale Score, 13–14), and low risk (Braden Scores > 14). The hypothesis of no group difference will be tested by examining whether the 95% confidence intervals of the rates of PrU and the 2-h repositioning overlap. If so, the hypothesis for no group difference will be confirmed. We will also determine how changes in medical severity components (as measured by a modified Comprehensive Severity Index), change in clinically assessed risk level (low, moderate, high as measured by the Braden Scale) and their interactions with repositioning schedule are associated with PrU development.

Descriptive statistics will be used to examine resident status, interventions, outcomes, and cost elements. For categorical variables, we will create contingency tables and use chi-squared or Fisher’s exact tests to determine the significance of bivariate differences. For continuous variables, we will use analysis of variance or non-parametric tests, depending on variable distributions. A two-sided *p*-value < 0.05 will be statistically significant. Intervention cost by NH and study arm and incremental cost-effectiveness ratios (ICERs) will be calculated and compared for cost per percentage reduction in PrUs. Sensitivity analysis will be conducted with the range of observed repositioning times, nurse salaries, and market prices for non-labor inputs to assess the robustness of the ICERs and their sensitivity to labor and non-labor input prices.

Because we will be examining PrU development from assessment to assessment, the rate of PrU incidence will be modeled as a binary outcome using repeated measures logistic regression and a specified working correlation matrix that models the correlation of responses within subjects. Full likelihood estimation methods are not appropriate for repeated measures logistic regression, so generalized estimating equations (GEEs) will be used instead with model fit assessed using the quasi-likelihood information criterion (QIC). Robust standard errors, clustered at the facility level, will be employed to account for covariance among residents within facilities over time. To test the robustness of models, we will also use non-linear mixed models using PROC GLIMMIX as another option for modeling the data (instead of GEEs using PROC GENMOD). With PROC GLIMMIX, we can use random effects to model the covariance rather than clustered standard errors. As predictors, we will include time-invariant resident characteristics, e.g., age, gender, Medicaid payer, and repositioning schedule, as well as time-varying characteristics, such as resident severity measure, risk level as determined by Braden Scale© score, staffing characteristics (e.g., number, mix, and turnover), and suggested MDS resident data elements as covariates. We may lag some time-varying resident characteristics by one assessment because we want to study the associations of repositioning time with PrU development, controlling for the starting point of the resident for that assessment interval. Interaction variables will be included in the predictor data set.

Residents without PrUs who drop out of the study after at least a three-day stay but before the conclusion of 4 weeks will be included in the analysis based on intent to treat. Residents who develop a Stage 3 or worse PrU, or deep purple discoloration, will be removed from the study per repositioning protocol, but will be considered a completed case if the ulcer developed on the coccyx, sacrum, trochanter or heel. Residents who develop ulcers on sites not thought to be influenced by bed position or limited mobility, or related to sitting, will continue to be followed for analysis, but will not be included in the NH-wide protocol.

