## Methods

The TEAM-UP study is a cluster randomized clinical trial with facility-level use of an assigned repositioning interval as the primary intervention and will be conducted at 9 NHs that are all using VE support surfaces. Each participating NH will be randomly assigned to one of three intervention arms. Each arm will have 3 NHs with each NH using a single, NH-wide repositioning interval at either 2, 3, or 4 h as standard of care during the 4-week intervention period. Randomization will occur at the facility level. The sequence in which the repositioning intervals are to be implemented will be randomly ordered and, then assigned to NHs inclusive of each arm of NHs. Thus, 3 clusters of 3 NHs are created with randomly sequenced repositioning intervals.

A secondary cluster is created within each NH as the NH implements its standard risk assessment protocol; residents will be clinically categorized forming clusters by level of risk for developing a new PrU. Level of risk categorization into 3 groups is defined by a Braden score of low (15–18), moderate (13–14), or high (10–12) [32]. All eligible residents will wear a wireless triaxial accelerometer sensor throughout the intervention as part of the NH’s standard of care. Residents may refuse the sensor and can decline to move when prompted by staff as part of their right to refuse care (see Fig. 1). This pragmatic approach offers a unique opportunity to study a single NH-wide repositioning schedule, thus avoiding the potential for staff confusion associated with resident-level random assignment to repositioning intervals, which would require staff to simultaneously execute multiple turning schedules.

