##### Statistical power.

According to previous research, the average PrU incidence rates range from 5.2–15%. At the time of study design, the nine NHs within the NHS were identified with the highest PrU incidence rates which averaged 9.2% (SD = 3.3%). In power analyses, we used 3.5% for PrU incidence as the expected rate for intervention since it is the highest rate found in the TURN study (for moderate-risk patients). The PrU incidence rates have been translated into an odds ratio of 0.38 (= 3.5%/9.2%) as the effect size to detect. For Aim 1, odds ratios from a logistic regression of PrU incidence rates in the three treatment arms (i.e., at 2-, 3-, and 4-h repositioning frequencies), controlling for risk level, are proposed to test the difference in PrU incidence rates between the 4-h arm and the 2-h arm as well as between the 4-h arm and the 3-h arm at 4 weeks; we are assuming that the distance between the 2-h arm and the TURN 3-h odds ratio will be larger. A sample size of *N* = 951 (*n* = 317 for each arm) will be required to detect an odds ratio of .38 with a power of 0.95 at a one-tailed significance level of α = 0.05, according to G*Power. We are using a power of 0.95 instead of the conventional power of 0.80 to ensure that we will have a smaller Type II error to test the hypothesis of no-group difference that we expect to fail to reject. We are using a one-tailed test since we are only interested in determining whether the PrU rate is higher for assigned repositioning intervals longer than the current 2-h standard practice.. For Aim 2, GEE is proposed. A sample size of *n* = 114 for each group (total *N* = 342) will be required to detect an effect size of 5.7% (= 9.2% - 3.5%) with a power of 0.80 at a one-tailed significance level of α = 0.05, using the algorithms GEESIZE developed by Dahmen, et al., on an autoregressive structure for residual correlations [48]. Since the nine NHs will be randomly assigned to the three treatment arms, risk level will be the only potential covariate to be controlled in the models, and this is already considered in the power analyses. Therefore, we will target a sample size of *N* = 951 (the larger of the two required sample sizes) for both aims while taking into account potential losses due to turnover, attrition, and exclusion criteria. While this proposed study may look like a non-inferiority or equivalence trial, we will run regular one-tailed superiority tests, because (as noted earlier) we are only interested in examining whether or not the PrU rate is higher for less frequent repositioning than for the standard 2-h repositioning. (We assume that 2-h repositioning was followed to produce the 9.2% average PrU incidence rate across our 9 study NHs, because that is the current standard of care). Also, according to Snapinn [49], non-inferiority trials have many controversial assumptions and limitations that need to be made or addressed, and that is beyond the control of our study. For incidence, it is difficult to specify a non-inferiority margin for PrU rates. Instead, we will test the hypothesis of no group-difference by examining whether the 95% confidence intervals of the odds ratios (for Aim 1) or the PrU rates (for Aim 2) of the two pairs of compared groups (e.g., 4-h arm vs. 2-h arm and 4-h arm vs. 3-h arm) overlap. If the confidence intervals do overlap, the hypothesis for no-group difference will be confirmed.

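### The bivariate tests take no account of home although homes are randomised, so arm comparisons made with them reject too often; whether the Aim 1 model accounts for home is left unreconciled

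*Protocol article*

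**What the plan says.** All references are to the protocol article.

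- **Methods.** "Randomization will occur at the facility level", and "Each arm will have 3 NHs with each NH using a single, NH-wide repositioning interval".
- **Quantitative analyses, opening paragraphs.** "Descriptive statistics will be used to examine resident status, interventions, outcomes, and cost elements". For categorical variables the plan will "use chi-squared or Fisher’s exact tests to determine the significance of bivariate differences". Then: "For continuous variables, we will use analysis of variance or non-parametric tests, depending on variable distributions". The threshold is fixed: "A two-sided *p*-value < 0.05 will be statistically significant". No allowance for home is attached, and the text does not say which groups are compared.
- **Quantitative analyses, modelling paragraph.** Ulcer incidence from assessment to assessment is modelled by repeated-measures logistic GEE with repositioning schedule among the predictors. Robust errors are clustered at the facility, and a random-effects model serves as a robustness check. No aim is named.
- **Statistical power.** "For Aim 1, odds ratios from a logistic regression of PrU incidence rates in the three treatment arms", controlling for risk level, are to compare 4 h with 2 h and 4 h with 3 h at 4 weeks. GEE is proposed for Aim 2. Risk level is described as the only potential covariate. The section gives incidence of 9.2% (SD 3.3%) across the nine homes, an expected 3.5%, and N = 951 (317 per arm). It commits both to one-tailed superiority tests and to a rule based on overlap of 95% intervals.

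**The concern.** A resident-level chi-squared, Fisher, ANOVA or ordinary logistic test takes its reference distribution from independent residents. Its null is therefore no arm difference and also no variation between homes. The hypothesis of interest is only the first part. With three whole homes in each arm, ordinary variation between homes appears as a difference between arms.

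The bivariate tests cover outcomes, baseline status and cost elements and carry a significance threshold, so chance differences between homes could be reported as effects of the repositioning interval. If the Aim 1 regression were also fitted without home, its odds-ratio intervals would be too narrow.

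**Working it through.** **1. The plan's own figure.** Take the large-sample formula for logistic regression with one binary predictor:

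N = [z₀.₉₅√v₀ + z₀.₉₅√v₁]² / (ln OR)²

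Inputs are base rate 9.2%, OR 0.38, one-tailed 0.05 and power 0.95. The predictor share is not stated; I assume 2/3 (two arms against one).

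- Odds 0.092/0.908 × 0.38 = 0.0385, so the second rate is 3.71% and the average rate is 5.54%.
- v₀ = 1/(0.0554 × 0.9446 × 2/9) = 86.0.
- v₁ = 1/(1/3 × 0.092 × 0.908) + 1/(2/3 × 0.0371 × 0.9629) = 77.9.
- N = [1.645 × (9.27 + 8.83)]² / 0.936 ≈ 947.

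A share of 1/3 gives 959. Both are close to 951, with independent residents and a design effect of 1.

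**2. Intracluster correlation (assumed; none is stated).** ICC = SD²/[p(1−p)], with m = 951/9 = 105.7 residents per home and design effect DE = 1 + (m−1) × ICC.

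- *Upper, all of the 3.3% is between homes:* 0.033²/(0.092 × 0.908) = 0.0130; DE = 1 + 104.7 × 0.0130 = 2.36.
- *Lower, one month's binomial noise removed:* 0.033² − 0.092 × 0.908/106 = 0.00030, an SD of about 1.7%; ICC = 0.0036; DE = 1.37.
- *At 3.5% with the same relative spread:* SD 0.66 to 1.26%; ICC 0.0013 to 0.0047; DE 1.13 to 1.49.

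**3. Actual size of tests that ignore home.** Three-arm chi-squared (2 df): exp[−5.99/(2·DE)]. Pairwise two-sided: 2[1−Φ(1.96/√DE)]. One-sided: 1−Φ(1.645/√DE).

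| Setting | DE | 3-arm chi-squared | Pairwise two-sided | Pairwise one-sided |
|---|---|---|---|---|
| 9.2%, upper | 2.36 | 28.2% | 20.2% | 14.2% |
| 9.2%, lower | 1.37 | 11.3% | 9.5% | 8.0% |
| 3.5%, upper | 1.49 | 13.4% | 10.8% | 8.9% |
| 3.5%, lower | 1.13 | 7.1% | 6.6% | 6.1% |

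Beta-binomial simulation (three homes of 106 per arm, no arm effect) agrees for chi-squared: 28% and 11% at 9.2%, 13% and 7% at 3.5%. The Wald test on the log odds ratio runs slightly below the formula. At 9.2% it rejects about 7.5 to 14% one-tailed and 8 to 19% two-sided. At 3.5% it runs from close to nominal up to about 9% two-sided. At the upper setting the two-sided rate of 19% means that 95% intervals cover about 81%. Fisher's test at 9.2% rejects about 7 to 16%.

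**4. The overlap rule.** Two unadjusted 95% intervals for the 4-h and 2-h arms fail to overlap in about 0.5% of trials with independent residents. With clustering the figure is about 1.5 to 7% at 9.2%, and about 0.5 to 2% at 3.5%.

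**5. Candidate remedies.** ANOVA on the nine home summaries (6 residual df) rejects about 5% in every setting above. Facility-clustered robust errors with a normal reference and no small-sample correction do not. With three homes per arm, the uncorrected ratio behaves roughly like a t variable on 4 df scaled by √(3/2), so the size is P(|t₄| > 1.96 × √(2/3) = 1.60) ≈ 18%. The common factor of 9/8 on the variance lowers this only to P(|t₄| > 1.70) ≈ 16%.

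**The case against.** **The bivariate tests are descriptive, and arms are not named.** True, and resident-level tests are reasonable for comparisons within homes. But the sentences follow directly on the three-arm hypothesis, include outcomes and fix a significance level. Nothing restricts them to within-home use.

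**Aim 1 is not stated to ignore home.** This stands. A reader might infer from the power section that the Aim 1 regression assumes independent residents: logistic regression and GEE are assigned to different aims, and N = 951 is approached with a design effect of 1. But the modelling paragraph describes a logistic model of incidence that contains the repositioning schedule, has facility-clustered errors, and is tied to no aim. The documents support only that the two places are unreconciled.

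**The size rests on an inferred correlation.** This also stands. The SD describes homes identified for high incidence, over a period not given, without adjustment for risk level, which Aim 1 controls. At 3.5% with sampling noise removed, the excess is small. No continuous or cost variable was simulated, so the figures apply to ulcer incidence only.

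**The interval-overlap rule is conservative.** Correct: its false non-overlap stays at about 7% or below. But the protocol also commits to one-tailed tests, where the inflation applies directly.

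**Conclusion.** The point holds for the bivariate tests wherever they compare arms. Under no arm effect, the three-arm chi-squared test on ulcer incidence rejects about 11 to 28% at 9.2% incidence (2.3 to 5.6 times nominal) and about 7 to 13% at 3.5%; Fisher's test is less affected. These figures assume that the stated SD reflects variation between homes, with ICC between about 0.004 and 0.013 at 9.2%.

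For Aim 1 the defect is an unreconciled description. The inflation of about 7.5 to 14% one-tailed or 8 to 19% two-sided at 9.2% follows only if the model is fitted without home. It would be wrong to apply a five-fold inflation to every test: that figure belongs to the three-arm chi-squared test at the upper ICC alone, while the planned one-tailed contrast reaches at most about 2.8 times nominal (14/5). The correction should be made, since it is cheap and the rule as written misstates significance.

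**What to change.** **Quantitative analyses.** Test arm differences on the nine home-level proportions or means, by ANOVA with 6 residual df or by a permutation test over the home allocations that the randomisation allowed. For one pair of arms there are at most 20 such allocations (6 choose 3), so the smallest two-sided p-value is 2/20 = 0.10; the permutation test therefore suits the three-arm comparison. Alternatively, report arm comparisons without p-values. Keep resident-level tests for within-home comparisons, such as residents with and without an ulcer, stratified by home.

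**Statistical power.** State that the Aim 1 odds ratios and intervals come from an analysis that accounts for home with a small-sample correction. This can be a home-level analysis, or a clustered or mixed model with corrected errors and t degrees of freedom based on the number of homes. Naming facility-clustered errors alone is not enough, since uncorrected they reject about 16 to 18% two-sided. Make the modelling paragraph say which aim it serves.

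**Cost.** Wording in two places and a few lines of code. Intervals widen by about √DE × 2.447/1.96 (the 6-df t value over the normal one): 1.46 times at DE 1.37 and 1.92 times at DE 2.36. P-values rise accordingly.
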